## Abstract

**Background:**

The recovery of balance function is a critical segment in the rehabilitation treatment of stroke. The cerebellum is considered as the key structure involved in balance and motor control. The cerebellar vermis plays an important role in integrating vision, proprioception, and sensory skin input and may be a candidate stimulation target for regulating the motor network related with balance. However, evidence that the intermittent theta burst stimulation (iTBS) of cerebellar vermis can promote the recovery of balance function after stroke remains insufficient. Therefore, this study aims to explore the efficacy of the cerebellar vermis iTBS for the treatment of balance function in patients with stroke.

**Methods and Analysis:**

Forty patients with stroke will be recruited in this prospective, randomized, sham-controlled trial. Participants will be randomized in a 1:1 ratio to receive either 15 sessions of cerebellar vermis iTBS (600 pulses) or sham stimulation. Additionally, a routine rehabilitation therapy follows the intervention. The primary outcome is the Berg Balance Scale, and the secondary outcomes are the Fugl–Meyer assessment of the lower extremity and modified Barthel index. The above outcomes will be assessed before intervention and at the end of each week. Pre- and post-iTBS resting-state functional magnetic resonance imaging (rs-fMRI) will be acquired, and the regional homogeneity, fractional amplitude of low-frequency fluctuation and functional connectivity will be calculated and analyzed.

**Discussion:**

This protocol holds promise as a potential method to improve balance function in patients with stroke. If the outcomes of patients improve after the intervention, the study will provide new insights into improving balance function.

**Ethics and Dissemination:**

This study has been approved by the Medical Research Ethics Committee of Wuxi Mental Health Center (Wuxi Tongren Rehabilitation Hospital). Results will be disseminated through (open-access) peer-reviewed publications, networks of scientists, professionals, and the public and presented at conferences.

**Clinical Trial Registration Number:**

www.chictr.org.cn, identifier ChiCTR2100052590.

## Introduction

Every year, over 15 million people in the world suffer from stroke (Van Lieshout et al., 2017). Balance problem is a common dysfunction that arises after stroke and is usually due to poor proprioception, decreased motor control, and abnormal integration of nervous system (Xiong et al., 2019). Moreover, the balance problem may be the main cause of poor walking ability and increased risk of falls in patients with stroke (Zhang et al., 2020). About 15–37% of patients with stroke fall down at least once due to balance dysfunction during hospitalization (Rabadi et al., 2012). Falls appear to be frequent after discharge, with approximately 40% falling within 6–12 months of stroke (Wada et al., 2007). Therefore, balance plays a significant role in the rehabilitation process of stroke. However, pharmacotherapy (Mead et al., 2013) and conventional rehabilitation treatments, including core strength exercises (Chung et al., 2014), visual feedback training (Zhang et al., 2020), neurodevelopmental therapy (Langhammer and Stanghelle, 2011), and proprioceptive neuromuscular facilitation (Eng and Tang, 2007) performed unsatisfactory results on balance recovery among stroke patients.

In recent years, repetitive transcranial magnetic stimulation (rTMS), a non-invasive brain stimulation technology, has been widely used in various nervous system diseases (Ren et al., 2019; Yin et al., 2020). rTMS induces a current in the cerebral cortex through a coil that generates a magnetic field, thereby regulating the excitability of the cerebral cortex and affecting neuroplasticity (Brown et al., 2021). Theta burst stimulation (TBS), a novel pattern of rTMS, has the characteristics of lower stimulation intensity and a shorter stimulation session (2–3 min or less) (Pinto et al., 2018), the relatively low stimulation intensity reduces the risk of adverse reactions especially the risk of epileptic seizures (Gutierrez-Muto et al., 2020). Huang and Rothwell (2004) were the first to investigate the neurophysiological effects of TBS in healthy human subjects, founded that 600-pulse intermittent TBS (iTBS) can enhance cortical excitability.

The cerebellum plays an important role in maintaining postural position, regulating the muscle tension associated with postural movements, and coordinating voluntary movements (Manto et al., 2011). To date, studies on the effects of cerebellar rTMS on balance rehabilitation are still limited. As pointed out in neurophysiological research, the cerebellar activity in patients with stroke is positively correlated with the recovery of walking function (Bijsterbosch et al., 2011). Low-frequency rTMS in the cerebellum can improve walking ability in patients with spinocerebellar degeneration (Svenja et al., 2017). Furthermore, a meta-analysis suggested that cerebellar stimulation may affect corticospinal excitability (Zelda et al., 2016). Koch et al. (2018) also found that the iTBS of the unaffected cerebellum promotes the excitability of the posterior parietal cortex and improves the balance and gait function in patients with chronic stroke (over 6 months).

Notably, the choice of the rTMS target has a remarkable influence on its therapeutic effect. However, an agreement on how to select the best targets for patients with balance dysfunctions is limited until now. Primary motor cortex (M1) area is one of the most common targets. Kim et al. (2014) used low-frequency rTMS to act on the M1 area of the patient’s lower extremities and found that the 10 min walking speed and Berg Balance Scale (BBS) are improved. Additionally, the supplementary motor area (SMA) (Richard et al., 2017) and dorsal prefrontal cortex (Harris et al., 2018) have been implicated to be critical in balance tasks. With deepening research, recent studies demonstrated that the cerebellum is also one of the effective targets of rTMS. The cerebellar vermis is a major part of the cerebellum. Notably, patients with cerebellar vermis lesions present with balance dysfunction (Harris et al., 2018), whereas cerebellar hemisphere lesions focus on global coordination dysfunctions (Carass et al., 2018; Maas et al., 2020). A recent study that used fNIRS technology found that after a single iTBS on the cerebellar vermis in healthy individuals, the HBO_2_ values in bilateral SMA regions are increased. These results indicated a potential link between the cerebellar vermis and SMA (Tan et al., 2021). The cerebellar vermis may be a new target for iTBS to intervene with balance function and deserves further exploration.

A randomized controlled clinical trial will be conducted to investigate the rehabilitation effect of the cerebellar vermis intervened by iTBS in stroke patients with balance dysfunctions. Furthermore, the resting-state functional magnetic resonance imaging (rs-fMRI) will be used to analyze the functional connections between cerebellar vermis and other areas of the cerebral cortex, and clarify the neural remodeling mechanism. We propose a hypothesis that iTBS of cerebellar vermis can promote the recovery of balance function after stroke. This study may provide new insights into the therapeutic efficacy and underlying neuroplasticity mechanisms of cerebellar vermis intervention.

## Materials and Methods

### Study Design

This study will be carried out in the Department of Rehabilitation, Tongren Rehabilitation Hospital, Wuxi, China. Before the conduct of formal experiments, a research coordinator who is responsible for recruitment will arrange a conversation with potential participants to discuss some details, including research purpose, procedures, and the potential risks and benefits. Once informed consent is signed by the patient or their legal guardians (if the patient cannot write independently or consider consent), a questionnaire and baseline assessment will be arranged.

All participants will be randomly assigned to real or sham iTBS and then receive routine rehabilitation treatment, and they will be assessed using the BBS, Fugl–Meyer assessment of the lower extremity (FMA-LE), and modified Barthel index (MBI). Moreover, rs-fMRI scans will be performed at baseline and 3 weeks after treatment. The study flow chart is shown in Figure 1. All baseline data gathering, follow-up assessment, and interventions will be carried out by well-trained researchers with the support of academic staff. This study has been approved by ethics committees (WXMHCIRB2021LLky132) and registered on www.chictr.org.cn on 27 October 2021 under the number ChiCTR2100052590. Details are shown in Table 1.

**FIGURE 1 F1:**
[figure not shown]
Study flow diagram. ^1^BBS, ^2^FMA-LE, ^3^MBI, and ^4^fMRI. TAU, treatment as usual; iTBS, intermittent theta burst stimulation. T0, before intervention; T1, at the end of first week of post-intervention; T2, at the end of second week of post-intervention; T3, at the end of third week of post-intervention.

**TABLE 1 T1:** Trial registration data.

Data category	Trial information
Primary registry and trial identifying number	ChiCTR2100052590
Date of registration in primary registry	27 October 2021
Secondary identifying numbers	N/A
Source(s) of monetary or material support	This project is being supported by Wuxi Taihu Talent Project (WXTTP2020008), the Nanjing Municipal Science and Technology Bureau (2019060002), the Major Scientific Research Project of Wuxi Health Committee (Z202013), Top Talent Support Program for Young and Middle-Aged People of Wuxi Health Committee (HB2020079), Scientific and Technological Development Fund from Wuxi Science and Technology Bureau (Y20212008), Wuxi Municipal Health Commission Scientific Project (T201144), and Jiangsu Geriatrics Clinical Technology Application Research Project (LR2021040).
Primary sponsor	N/A
Secondary sponsor(s)	N/A
Contact for public queries	[name], [contact]
Contact for scientific queries	[name], [contact]
Public title	Effect of cerebellar vermis iTBS on the balance dysfunction of stroke patients and the brain remodeling mechanism
Scientific title	Effect of cerebellar vermis iTBS on the balance dysfunction of stroke patients and the brain remodeling mechanism
Countries of recruitment	China
Healthy conditions(s) or problem(s) studied	Stroke with hemiparesis, including balance dysfunction
Intervention(s)	Active comparator: iTBS (application of 600 pulses with a frequency of 50 Hz, in a theta-rhythm of 5 Hz for 200 s) will be applied to the cerebellum vermis positioned tangentially to the scalp combined with routine rehabilitation treatment. Sham comparator: Sham stimulus will be applied to same location with a customized sham coil, also combined with routine rehabilitation treatment.
Key inclusion and exclusion criteria	Inclusion criteria: (a) have a diagnosis of stroke confirmed by CT and/or MRI, (b) have their first-ever unilateral ischemic stroke between 1 and 6 months of onset, (c) are 40–75 years old, (d) presented with a balance dysfunction with a Berg score between 0 and 40, (e) can follow simple verbal commands or instructions, and (f) can cooperate in signing informed consent forms. Exclusion criteria: (a) with contraindications involving TMS and fMRI (e.g., intracranial implant, cardiac pacemaker, implanted drug pumps, and pregnancy), (b) with cerebellum or brainstem stroke, (c) with balance dysfunction before stroke, (d) with serious diseases that may contribute to condition progression, (e) with severe deficits in communication or executing commands that prevent cooperation with assessment and treatment, (f) who are taking psychotropic drugs, and (g) who are currently enrolled in other clinical trials.
Study type	Interventional Allocation: randomized intervention model Masking: participants and assessors-blinded Assignment: parallel Primary purpose: treatment
Date of first enrolment	Not yet started
Target sample size	40
Recruitment status	Recruiting
Primary outcome(s)	Berg balance scale
Key secondary outcome(s)	Lower extremity of the Fugl–Meyer assessment; modified Barthel index; regional homogeneity, fractional amplitude of low frequency fluctuation and functional connectivity analyses from rs-fMRI.

### Participants

#### Inclusion Criteria

The inclusion criteria are as follows. Participants who (a) have a diagnosis of stroke confirmed by CT and/or MRI, (b) have their first-ever unilateral ischemic stroke between 1 and 6 months of onset, (c) are 40–75 years old, (d) presented with a balance dysfunction with a Berg score between 0 and 40, (e) can follow simple verbal commands or instructions, and (f) can cooperate in signing informed consent forms.

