### Sample Size

The sample size was calculated using a G*power of 3.1.4. The effect size was calculated as 0.28 based on the BBS from a study reported by Koch et al. (2018). To achieve 95% power with an alpha error of 5%, a sample size of 30 patients will be required. Allowing for a dropout rate of 20%, at least 38 patients are necessary. To ensure enough power to detect this typical difference, we will aim to recruit 40 patients (20 patients per group).

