### Randomization

All participants will be prestratified into two subgroups (i.e., poor balance on 0–20 scores vs. acceptable balance on 21–40 scores) on the basis of their balance function to ensure a relatively even distribution between groups (Lisa and Nicol, 2008) (Figure 2). After obtaining informed consent, a random sequence will be generated using the computer, 40 participants will be randomly allocated in a 1:1 ratio to each group and will receive either real or sham iTBS. The advantage of this type of assignment process, which is designed in our study, is that detect effects can be improved especially for studies involving small samples.

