### Statistical Analysis

#### Clinical Data Analysis

The SPSS (version 22.0, Chicago, IL, United States) statistical software will be used for data analysis. The difference will be considered statistically significant when the *P*-value ≤ 0.05 in two-tailed test. The assumption of normality will be verified by normal probability plots and the Shapiro–Wilk test. Continuous variables with normal distribution will be described as the mean (standard deviation) and analyzed by an independent-samples *t*-test. For abnormally distributed variables, the data will be described as medians with ranges and compared by Mann–Whitney U test (non-parametric tests). Categorical variables will be expressed as frequency (percentage) and Chi-square test or Fisher’s exact test will be used. Repeated measures analysis of variance (ANOVA) will be used to analyze value changes of BBS, FMA-LE, and MBI across four testing time points (weeks 0, 1, 2, and 3). When the interaction is significant, *post hoc* analysis will be conducted, and the Bonferroni adjustment will be used for paired comparisons. Data on clinical scales will be based on per-protocol (PP) and intention-to-treat (ITT) analyses (Sanchez and Xun, 2010). The PP is usually defined as subjects who complete at least 80% of the treatment protocol (Zhao et al., 2021). An ITT analysis include all the patients recruited in the study, irrespective of whether they completed the study period or not. The missing values will be imputed using a multiple imputation method.

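### Time since stroke onset (1–6 months) is neither stratified on nor used in the stated repeated-measures ANOVA; adding it as a covariate would be a cheap gain in precision and protection against an unlucky allocation

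*Protocol article*

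**What the plan says.** - **Eligibility** (Inclusion Criteria, repeated in Table 1): patients must "have their first-ever unilateral ischemic stroke between 1 and 6 months of onset", a five-month span.
- **Randomisation**: the only stratification factor is baseline BBS, split as "poor balance on 0–20 scores vs. acceptable balance on 21–40 scores". The section then says that "40 participants will be randomly allocated in a 1:1 ratio to each group".
- **Efficacy analysis** (Clinical Data Analysis): "Repeated measures analysis of variance (ANOVA) will be used to analyze value changes of BBS, FMA-LE, and MBI across four testing time points", at weeks 0, 1, 2 and 3. No covariate is named. Simple two-group tests are listed for continuous variables, with two-sided significance at 0.05.
- **Heterogeneity** (Discussion): the article raises the wide spread of balance function among those enrolled and answers it with the BBS strata. It does not mention time since onset there.
- **Planning source** (Introduction and Sample Size): the effect size of 0.28 comes from a study whose patients the article describes as chronic, more than 6 months after stroke. This trial's window ends where that population begins.

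**The concern.** The hypothesis is about recovery, so the efficacy signal is a difference between arms in change over three weeks. For such a signal, a baseline variable that predicts change matters at least as much as one that predicts level. BBS strata balance level. They cover time since onset only as far as the two are correlated, and two patients with the same BBS can be at opposite ends of the 1–6 month window.

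If time since onset predicts 3-week change, leaving it out has two consequences:

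1. Its share of the variance stays in the error term for BBS, FMA-LE and MBI, and power is lost.
2. With 20 per arm, chance can leave the arms noticeably different in mean onset time. In that realised trial, part of the group-by-time contrast would reflect onset time and not iTBS.

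The Randomization section itself justifies stratification by the small sample. The same reasoning applies to a variable that must be established for every patient at screening.

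**Working it through.** **Plan's own figure.** The stated 30 patients reproduce as a within-between interaction in a repeated-measures ANOVA with f = 0.28, 2 groups, 4 time points, correlation 0.5 and sphericity (the last two assumed, not stated):

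- λ = f²·N·m/(1 − ρ) = 0.0784 × 30 × 4/0.5 = 18.8
- degrees of freedom 3 and (30 − 2) × 3 = 84; power 95.9%
- dropout: 30/0.80 = 37.5, rounded up to 38; target 40

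The present point does not touch that calculation.

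**Inputs for this point.** From the article: a window of 1–6 months, 20 per arm, two-sided 0.05. Assumed, because the article gives no figure: onset times uniform over the window; share of variance in BBS change explained by onset time, R² = 0, 0.1, 0.2 or 0.3; true effect 0.9 SD of BBS change.

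**Step 1: chance imbalance.**

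- SD of onset time = 5/√12 = 1.443 months
- SE of the arm difference in means = 1.443 × √(2/20) = 0.456 month; 95% range ±1.96 × 0.456 = ±0.89 month
- P(gap > 0.5 month) = 27%; P(> 0.75 month) = 10%; P(> 1 month) = 3%
- expected absolute gap = 0.456 × 0.80 = 0.36 month
- P(standardised difference > 0.5, i.e. 0.5 × 1.443 = 0.72 month) = 11%

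**Step 2: effect on the comparison.** Two-group comparison of BBS change, 40,000 simulated trials per setting, with and without onset time as a linear covariate. Simple randomisation was used; the BBS strata were not modelled.

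| R² | Overall type I error, unadjusted | Power, unadjusted | Power, adjusted |
|---|---|---|---|
| 0 | 5.0% | 79% | 78% |
| 0.1 | 5.1% | 79% | 82% |
| 0.2 | 4.9% | 79% | 86–87% |
| 0.3 | 4.9% | 79% | 90% |

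The 79% belongs to this simplified comparison and the assumed 0.9 SD. It is not an estimate of the trial's power and does not contradict the stated 95%. Only the change between the last two columns is of interest.

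**Step 3: given an unlucky allocation** (standardised difference above 0.5, about 11% of allocations).

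| R² | Shift at a difference of 0.5 (0.5 × √R²) | Type I error, unadjusted | Type I error, adjusted | Power, unadjusted |
|---|---|---|---|---|
| 0.1 | 0.16 SD | 8% | 4.7% | 76% |
| 0.2 | 0.22 SD | 11% | 5.1% | 73% |
| 0.3 | 0.27 SD | 15% | 4.8% | 69% |

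At R² = 0 there is no shift and nothing to protect against.

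**The case against.** **Bias.** A reader might infer that uneven spontaneous recovery can be mistaken for an iTBS effect, or hide one, in this design generally. The documents do not support that. The trial is randomised with a concurrent sham arm, blinded patients and assessors, and the same routine rehabilitation in both arms. Onset time is balanced in expectation, the unadjusted estimate is unbiased, and type I error is near 5% at every R² tried. The inflated figures in step 3 hold only given a bad draw, and the overall 5% already averages over such draws. This objection stands in full and limits the point to precision and conditional protection.

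**The gradient.** It is also tempting to state as fact that recovery differs widely between 1 and 6 months. No section gives a recovery rate by onset time. The chronic population of the reference study shows that the planning source lies outside this window; it says nothing about variation inside it. The size therefore remains an assumption, and R² = 0 belongs in the range.

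**Unseen plan.** A covariate list is often left to an analysis plan, which may exist. That is why this is not an error or a contradiction in the article. What remains is that the article states its model and its single stratification factor, with reasons, and one specific variable could improve that model at almost no cost.

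**Why this factor?** Age (40–75) is not stratified either, and few strata are sensible with 40 patients. That is a fair reason not to add a stratum, and none is proposed. The BBS strata may also capture part of the onset effect, which would reduce the gain.

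**Conclusion.** The point holds as a worthwhile improvement to the design. The article contains no mistake here. The 1–6 month window, the single BBS stratifier and the covariate-free ANOVA are all as described, so a plausible predictor of 3-week change goes unused.

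The gain from adjustment is about 3, 7–8 or 11 percentage points of power if onset time explains 10, 20 or 30% of the variance in BBS change, and a loss of about 1 point if it explains none. There is also protection in the roughly one allocation in nine where the arms differ by more than half a standard deviation in onset time. These figures rest on the uniform onset distribution, the assumed R² range, the assumed 0.9 SD effect, a linear relation, and simple randomisation at 20 per arm. They do not support a claim of systematic bias or of a raised overall false-positive rate.

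**What to change.** Before unblinding, pre-specify time from stroke onset to randomisation as a covariate in the BBS, FMA-LE and MBI analyses. Choose one form and fix it, for example log days; allowing both days and log days would leave a choice open after the data are seen. In the repeated-measures model, include its interaction with time, because a main effect alone adjusts the level and not the change over the four assessments. Leave the BBS strata and the sample size as they are. If an analysis plan already contains this covariate, no change is needed.

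The cost is one sentence in the analysis section and a few degrees of freedom: with 40 patients and four time points, the within-patient error term goes from (40 − 2) × 3 = 114 to (40 − 3) × 3 = 111. No new data item is needed, because the eligibility criterion already requires the timing of the stroke. If the variable proves non-prognostic, the loss is about one percentage point of power (79% to 78% in the setting above). Fixing it in advance also removes the temptation to decide on adjustment after seeing the baseline table.

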#### Exclusion Criteria

Participants (a) with contraindications involving TMS and fMRI (e.g., intracranial implant, cardiac pacemaker, implanted drug pumps, and pregnancy), (b) with cerebellum or brainstem stroke, (c) with balance dysfunction before stroke, (d) with serious diseases that may contribute to condition progression, (e) with severe deficits in communication or executing commands that prevent cooperation with assessment and treatment, (f) who are taking psychotropic drugs, and (g) who are currently enrolled in other clinical trials will be excluded from the study.

